## Methods/design

### Design

The PRODECIDE-RCT is a randomized controlled superiority trial with two parallel groups, a 1:1 randomization and a six-month follow-up. Together with the trial, qualitative methods will be used to achieve in-depth understanding of the implementation processes. Additional e-learning modules will be developed and tested for usability.

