**Fig. 1 Fig1:**
[figure not shown]
Study Flow

Due to the nature of the intervention, blinding of the participating legal representatives and the researchers conducting the education program is not possible. Independent persons and an external biometrician, blinded to the group allocation, will perform data entry and data analysis, respectively.

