### Outcomes

The primary outcome measure is *knowledge*, which is operationalized as an understanding of decision-making processes in healthcare affairs and in setting realistic expectations regarding probabilities of benefits and harms of PEG, PR and AP to people with dementia.

Secondary outcome measures are: 1) legal representatives have obtained sufficient knowledge (using a cut-off of 70% correct answers in the knowledge test); 2) legal representatives have obtained sustainable knowledge, which is measured 6 months after intervention; 3) percentage of persons concerned affected by PEG, FEM or AP during follow up of 6 months; and 4) result of the first decision after intervention regarding PEG, PR and AP for the persons concerned including time to first decision.

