### Data analysis

Data will be entered into a SPSS database and double-checked by student assistants blinded to the group allocation. Simple plausibility checks will be done in the study center before the final statistical analysis by the statistician. Analysis of all quantitative data will use the intention-to-treat principle. Missing values in primary and secondary outcomes will be imputed using simple methods. A dropout analysis comparing baseline parameters between the study population and early dropouts (before T2) will be performed.

All statistical tests are two-sided using a significance level of 5%. Baseline parameters are described by frequency tables, means, standard deviations or quartiles.

The primary outcome is the percentage of correct answers for the knowledge test at T1. Assuming approximate normal distribution, the expected values from the IG and CG will be compared with adjustment for stratified randomization by professionals and volunteers using bifactorial analysis of variance (linear model). Distribution assumptions will be investigated by graphical methods. Furthermore, interactions between intervention and professional status will be included in a secondary model. Different effects depending on the professional status will be discussed.

The secondary outcome of sufficient knowledge (binary) at T1 will be compared between IG and CG using bivariate logistic regression, including IG/CG and professional status as independent variables. Additionally interactions between intervention and professional status will be investigated in a second model.

The sustainability of knowledge will be investigated at T3. The time course of the knowledge between T1 and T3 will be analyzed by fitting a linear mixed model: the dependent variable is knowledge (% of correct answers), and the independent variables are IG/CG, time (T1, T3), interaction between intervention and time, professional status and interaction between intervention and professional status. To adjust for repeated measurements of the legal representatives, random effects are included (covariance pattern model with covariance structure compound symmetry).

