Further secondary outcomes are the numbers of persons concerned and the percentage of these persons affected by PEG, FEM or AP (separately) per legal representative at T3. Mean values ± standard deviations will be described for IG and CG at T3 as well as at T0. Linear models will be fitted including IG/CG and initial values at T0 as independent variables.

Finally, the results of the first decision about PEG, FEM or AP by the legal representative after T0 (e.g., after training for IG, or after randomization for CG) will be assessed. Initially, the duration from T0 to the first decision will be described for IG and CG by Kaplan-Meier curves. In case of no decision, durations are censored at the end of observation after 6 months or at dropout. Kaplan-Meier curves between both groups will be compared by the log rank test, as long as there are no clear deviations from the proportional hazard assumption in the graphics. Four categories of decisions will be described by frequency tables.

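### The log-rank test for time to first decision is made conditional on an undefined visual check of proportional hazards, which its validity does not require

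*Protocol article*

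**What the plan says.** Secondary outcome 4 in the Outcomes section is the "result of the first decision after intervention regarding PEG, PR and AP for the persons concerned including time to first decision". For the time component, the Data analysis section says that "the duration from T0 to the first decision will be described for IG and CG by Kaplan-Meier curves", and that where no decision is made "durations are censored at the end of observation after 6 months or at dropout". The curves of the two arms are then "compared by the log rank test, as long as there are no clear deviations from the proportional hazard assumption in the graphics".

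The article does not say what makes a deviation clear, and it names no other test or effect measure if the check fails. The content of the decisions is not tested: "Four categories of decisions will be described by frequency tables". All tests are two-sided at 5%. On who makes the judgement, the section on randomization and blinding states: "Independent persons and an external biometrician, blinded to the group allocation, will perform data entry and data analysis, respectively".

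**The concern.** The log-rank null hypothesis is that the two time-to-decision distributions are equal. If it is true, the hazard ratio is 1 throughout and proportionality holds trivially. Non-proportional hazards can only arise when the groups differ. They then change the power of the test and whether a single hazard ratio describes the effect, but not the 5% level.

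The plan nevertheless lets a look at the outcome by arm decide whether the test is done. The test may therefore be missing in just the cases where a one-off course has an effect that comes early and fades. It may also be missing where the effect comes late, as could happen if the clock starts at baseline and training follows some time later. Because no replacement is named, the trial would then either have no group comparison for this outcome or have one chosen after the curves were seen.

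**Working it through.** **1. Inputs.** From the article: two-sided 5%, 1:1 allocation, six-month follow-up with censoring there or at dropout, and 86 analysed per group. The 86 was derived for the knowledge outcome and can be reproduced: 2 × (1.960 + 1.282)² × (0.17/0.085)² = 2 × 10.51 × 4 = 84.1, so 85 by normal approximation; the t-test gives 85.03, so 86. Then 86/0.8 = 107.5, rounded up to 108 per group, or 216. It serves below only as the arm size. The article gives no event rate, hazard or power for time to first decision, so those below are assumptions.

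**2. Does the test need the assumption?** The statistic is Z = Σ(O₁ⱼ − E₁ⱼ)/√ΣVⱼ with E₁ⱼ = dⱼ × Y₁ⱼ/Yⱼ, where dⱼ is the number of events at time j and Y₁ⱼ/Yⱼ is the intervention arm's share of those at risk. With no group difference, an event at time j falls in that arm with probability Y₁ⱼ/Yⱼ whatever the shape of the common hazard, provided censoring is unrelated to the decision. Simulated null trials (8,000 per shape, 86 per arm, about 10% dropout) rejected in 4.7% (constant hazard), 5.1% (decreasing), 5.0% (increasing) and 4.9% (piecewise).

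**3. Real effects, with a formal proxy for the eye.** The visual check is replaced by a 5% score test for a trend in the hazard ratio. Hazards are per month, for the first 2 months and then to month 6. Power under the rule is P(check passed) × P(reject given passed).

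| Assumed effect | Control | Intervention | Test dropped | Power, always run | Power under the rule |
|---|---|---|---|---|---|
| Proportional, HR 1.6 | 0.12, 0.12 | 0.192, 0.192 | 5% | 64% | 0.950 × 0.639 = 61% |
| Early | 0.12, 0.12 | 0.30, 0.12 | 42% | 72% | 0.578 × 0.736 = 43% |
| Late | 0.12, 0.12 | 0.12, 0.24 | 29% | 58% | 0.708 × 0.578 = 41% |
| Crossing | 0.12, 0.25 | 0.25, 0.12 | 90% | 5.5% | 0.099 × 0.062 = 0.6% |

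**4. A fading effect, with a crossing rule for the eye.** Hazard ratio 2.5 for 6 weeks, then 0.7. The test is dropped if the curves cross by at least c points in each direction. Across the assumed event rates it is dropped in about 28–36% of trials at c = 2, 11–13% at c = 5 and 1–3% at c = 10. For scale, 2 points of 86 is 1.7 people. The standard error of a difference near 50% is √(2 × 0.25/86) = 7.6 points, so 2 points is about a quarter of one standard error.

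**5. False positives.** Null trials; the three crossing rules and the unconditional test are shown at 30/50/70% with a first decision by 6 months.

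| Check | Test dropped | Rejection among tests run |
|---|---|---|
| Crossing, 2 points | 56/66/73% | 8.1/10.1/12.1% |
| Crossing, 5 points | 6/18/28% | 4.7/5.5/6.8% |
| Crossing, 10 points | 0.0/0.7/2.1% | 4.5/4.8/5.3% |
| Trend test (four hazard shapes) | about 5% | 4.8–5.1% |
| None (always run) | – | 4.5/4.8/5.2% |

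A repeat run gave somewhat higher figures for the two narrower rules: up to 79% dropped and 13.8% rejecting at 2 points, and up to 36% and 7.3% at 5 points. Counting all null trials, with a dropped test as no rejection, the 2-point rule gives 0.439 × 0.081 = 3.6%, 0.342 × 0.101 = 3.5% and 0.273 × 0.121 = 3.3%, all below 5%. If the better of an early-weighted and a late-weighted test is picked after a failed trend check, the overall rate becomes 5.9–6.3%.

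**The case against.** Four points can be made for the plan.

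- **False positives.** A reader might infer that reported p-values are significant too often under the null. The documents do not support that as a flat statement, because they do not say how the plots are judged. Inflation is material only if crossings of a couple of people count as clear. It is small at 5 points and absent at 10 points or with the trend test. As written, the rule lowers the overall rate, since it names no substitute. This objection stands.
- **Transparency.** A reader might call this selective reporting. The rule is disclosed in advance, the Kaplan-Meier curves are to be described whatever the check shows, and the analyst is blinded to allocation. That limits steering towards one arm. It does not remove the dependence on the data, because the two curves are still seen apart.
- **Caution about non-proportional curves.** It has some basis. In the fading scenario of step 4 the unconditional log-rank test had only 11–47% power, and with crossing hazards it had almost none. That argues for adding a summary that copes with such shapes, not for cancelling a valid test.
- **Scope.** This is the last of four secondary outcomes and plays no part in the sample size. A separate analysis plan might supply a criterion and a fallback. The condition itself is stated in the article, however, and rests on an assumption the test does not need.

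**Conclusion.** The condition should go. It ties the only planned group comparison of time to first decision to an unspecified reading of the outcome curves, for the sake of an assumption that matters for power and interpretation but not for validity. The harm is that the test can be lost when a real effect is non-proportional. The loss is 29% of trials for a late effect and 42% for an early one with the trend-test proxy, and anywhere from about 1% to 36% for a fading effect as the crossing rule narrows from 10 to 2 points.

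These sizes rest on 86 per arm, assumed hazards and dropout, and assumed stand-ins for visual judgement. The direction does not depend on them, but the magnitude does. A raised overall false-positive rate is not shown unless an unplanned test is substituted after a failed check. The primary knowledge analysis is unaffected.

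**What to change.** Delete the condition and state that the log-rank test is always performed. Keep the plots, and any look at proportionality, for interpreting the result. Prespecify one between-group summary that does not depend on hazard shape, such as the difference at 6 months in restricted mean time to first decision or in the cumulative proportion with a decision, with a 95% confidence interval. Name which one before the data are seen.

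The cost is one changed sentence and one extra estimate for a secondary outcome. No further data or participants are needed.

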### Sample size

No information was available for the primary outcome from previous studies. The assessment instrument was pretested with a before-after design to roughly estimate the expected intervention effect in the primary outcome of knowledge (given as a percentage of correct answers). The knowledge test was revised after three courses with a total of 18 legal representatives. Afterwards, two pilot courses with 16 participants were used to estimate the effect size of the intervention. Fifteen datasets before intervention, and 12 after intervention, were included in the analysis.

A common standard deviation of σ = 0.17 can be assumed in IG and CG. A mean difference of 0.085 between IG and CG can be detected by a power of 90% by the two-sided t-test, using a significance level of 5% based on a sample size of 86 per group (172 overall). Including a maximum dropout rate of 20%, an overall sample size of 216 is planned. The pilot study estimated a larger effect (0.38). Because of the low sample size, and considering a possible bias in the pilot study, the planned sample size is higher than theoretically necessary. It corresponds to a medium effect of 0.5*σ, as suggested by Cohen.

With six to ten participants per training session, the education program will be offered approximately 24 times (12 times per group).

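### The primary ANOVA and the t-test sample size treat all participants as independent, although only the intervention group is taught in about 12 shared courses before the T1 test

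*Protocol article*

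**What the plan says.** Legal representatives are randomised individually (Design: "two parallel groups, a 1:1 randomization and a six-month follow-up"). Under Interventions, the intervention group (IG) attends a 10-hour group programme, generally over two days, with case studies and discussion, and the same two persons conduct every session. The control group (CG) receives standard care and is invited to a course only after data collection is complete. Under Data collection, IG members receive the T1 test when the course ends and may complete it at once or return it by mail within two weeks.

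On grouping, the Sample size section states: "With six to ten participants per training session, the education program will be offered approximately 24 times (12 times per group"). On power it states: "A mean difference of 0.085 between IG and CG can be detected by a power of 90% by the two-sided t-test", with "A common standard deviation of σ = 0.17 can be assumed in IG and CG" and "using a significance level of 5% based on a sample size of 86 per group (172 overall"). It continues: "Including a maximum dropout rate of 20%, an overall sample size of 216 is planned".

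For the primary outcome, Data analysis states that "the expected values from the IG and CG will be compared with adjustment for stratified randomization by professionals and volunteers using bifactorial analysis of variance". The only random effect named there is for repeated measurements of the same representative in the T1–T3 model. Neither section mentions a course term, an ICC or a design effect.

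**The concern.** At T1 the IG consists of about 12 taught groups and the CG of ungrouped individuals. This is a partially nested design. People who sit through the same sessions share the group's discussion and whatever happened in that delivery. The Process evaluation section itself plans to record module completeness, deviations and unexpected difficulties for the training. If such features move scores, the IG mean varies more than 86 independent scores would imply.

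An ANOVA with arm and professional status does not see that extra variance. Its standard error would be too small, its confidence interval too narrow and its type I error above 5%. A valid test would have less than the stated 90% power. The T1 logistic model and the T1–T3 mixed model leave out the same term. Because both the model and the sample-size method are written out, this is a stated choice and not a detail left to an analysis plan.

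**Working it through.** **Inputs.** From Sample size: SD 0.17, difference 0.085, 86 per group analysed, 216 planned (108 per group), 12 courses per group. From Data analysis: two-sided 5%. The ICC is not in the protocol, so 0.01 to 0.10 is assumed.

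**1. The plan's own figure.** With 0.085/0.17 = 0.5 and independent observations, the noncentral t gives power 0.8999 at 85 per group and 0.903 at 86, hence 86. Then 86/0.8 = 107.5, rounded up to 108 per group, or 216. The plan's figures reproduce, with a design effect of exactly 1.

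**2. Clustering in the IG only.** Mean analysed course size is m = 86/12 = 7.17.

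- Design effect in the IG: DE = 1 + (m − 1) × ICC
- Standard error: SE = 0.17 × √((DE + 1)/86). With independence it is 0.17 × √(2/86) = 0.0259.
- SE ratio, true to planned: √((DE + 1)/2)
- Power, normal approximation: Φ(0.085/SE − 1.960)
- Power, noncentral t with Satterthwaite df = (DE + 1)² / (DE²/11 + 1/85)
- Type I error of the planned test: 2 × P(Z > 1.974/SE ratio), where 1.974 is the t critical value on 170 df

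Worked at ICC 0.05: DE = 1 + 6.17 × 0.05 = 1.31. SE = 0.17 × √(2.308/86) = 0.02785. The ratio 0.085/0.02785 is 3.05, so power is Φ(1.09) = 0.863. With df 31.8, power is 0.841.

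| Assumed ICC (IG only) | DE | SE ratio | Power, normal | Power, Satterthwaite | Type I error of planned test |
|---|---|---|---|---|---|
| 0.01 | 1.06 | 1.015 | 89.8% | 88.2% | 5.2% |
| 0.02 | 1.12 | 1.030 | 88.9% | 87.2% | 5.5% |
| 0.05 | 1.31 | 1.074 | 86.3% | 84.1% | 6.6% |
| 0.10 | 1.62 | 1.144 | 81.8% | 79.0% | 8.4% |

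The type I formula runs slightly low. A simulation of 40,000 trials with 12 courses of 7 or 8 gave 6.9% at ICC 0.05 and 8.8% at ICC 0.10. The planned standard error is too small by 1 − 1/1.074 = 7% and 1 − 1/1.144 = 13% at those two values.

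**3. If nobody drops out.** With 108 per group, m = 9 and ICC 0.05, DE = 1.40 and SE = 0.17 × √(2.40/108) = 0.0253. Power is 91.8% (90.1% with Satterthwaite df). The SE ratio is √(2.40/2) = 1.095, so the standard error remains too small.

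**4. Variance shared by both arms.** If an ICC of 0.05 belonged wholly to an institution or recruitment batch that supplies both arms equally, it would cancel from the arm contrast. The true SE would be √0.95 = 0.975 of the planned one, and the type I error 2 × P(Z > 1.974/0.975) = 4.3% (about 4.5% by simulation). The planned test would then be slightly conservative.

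**The case against.** The strongest reply is that the within-course ICC may be very small. The same two people teach every session from one curriculum and one set of materials already tested for feasibility, and the outcome is a multiple-choice test. This removes most trainer and content variation. It stands as a reason to include 0.01 in the range, where the loss is immaterial. It does not show that the ICC is zero.

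Second, a reader might count every difference between sites and dates as IG clustering. The documents do not support that. Recruitment runs through cooperating institutions around advertised course appointments, and randomisation follows individually, so a batch probably supplies both arms. Step 4 of the working shows that such shared variance does not inflate the error. Only variance that arises inside the course does.

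Third, a reader might infer that the trial is underpowered. That is also unsupported. The 20% dropout is a stated maximum, and T1 falls within two weeks of the course. The pilot effect was 0.38, at which power is about 100% at every ICC tried. The plan, however, distrusts the pilot for its small size and possible bias and chose 0.085, so the power statement should be right for that value. A large effect also does not repair an interval that is too narrow.

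Finally, it is tempting to say that most IG members take the test in the room. The protocol allows mail return and gives no proportion.

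**Conclusion.** The point holds in conditional form. The protocol creates grouping in one arm and then fixes a primary model and a power calculation that ignore it. The direction follows for any positive variance arising within courses. The size depends on an ICC that the protocol does not give: negligible at 0.01, and at 0.10 a power of about 79–82% and a type I error above 8%, both at 86 per group. It would go too far to state as fact that the power is overstated or the error inflated by a given amount, or to conclude that the sample is too small. Severity: should-fix.

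**What to change.** - **Data.** Record a course identifier for every IG participant and, for both arms, the institution or course appointment around which the person was recruited.
- **Primary model.** Replace the two-factor ANOVA with a partially nested linear mixed model: fixed arm and professional status, a random course effect in the IG only, arm-specific residual variance and small-sample degrees of freedom. Where both arms are recruited around the same appointment or institution, add that batch or institution as a term common to both arms, so that shared variance is not charged to the IG alone.
- **Secondary models.** Carry the course term into the T1 logistic model and the T1–T3 mixed model.
- **Power statement.** Say that 90% at 86 per group assumes independence. Add the range for assumed ICCs of 0.01 to 0.10 and the figure for 108 per group.

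The cost is one or two identifiers in the database and revised analysis wording. No participants are added. Intervals become slightly wider and the stated power slightly less favourable. Even with no clustering at all, the Satterthwaite degrees of freedom take power at 86 per group to about 89%.

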### Monitoring

A data monitoring committee will not be necessary, as the clinical trial does not involve a high-risk intervention and participants do not belong to a vulnerable population. We do not expect adverse events or other unintended effects of the intervention. During the entire study period, participants will have the possibility to contact the training experts.

### Process evaluation

To allow the study results to be generalized and to support future implementation, a comprehensive analysis of the underlying processes of this complex intervention is indispensable [42]. Barriers and facilitators of implementation should be assessed. Additionally, the high quality of the education program should be ensured. We will focus on parameters such as recruitment, reasons for participation or non-participation, intervention fidelity, structure- and process-related factors, attitudes toward the intervention, response of individuals and organizations and unintended consequences [42, 43].

Mixed methods will be applied [44] according to the MRC guidance for process evaluation of complex interventions [42].

Structured documentation will be used to assess data of recruitment and intervention fidelity (e.g. recruitment process; numbers of persons invited, responses and participants in each module; location, time and duration of the training; completeness of modules and reasons for deviations; and unexpected difficulties).

Recruitment and conducting the education program will be performed in cooperation with the participating institutions, which are experienced in offering training. Standardized interviews will be conducted with coordinators from these institutions to explore barriers and facilitators of implementation.

Feasibility and acceptance of the education program will be assessed at the end of each training session in a feedback round. All participants will be invited to take part, and statements from the feedback round will be documented.

In the IG (theoretical sampling), semi-structured interviews will be conducted. Relevant factors for acceptance and usability of the educational contents and materials may be further assessed. In particular, the use of educational contents in daily routines will be explored. Participants will be asked to describe a decision-making process, the roles of persons involved and their perceived changes in this process after the education program. If participant consent is provided, interviews will be audio recorded and then transcribed.

To gain further inside into behavioral changes, intermediate outcomes (e.g. number and content of conversations with healthcare professionals) will be assessed in a random sample of legal representatives (from both IG and CG).

Quality standards will be derived from existing standards in the field of continuing education [45, 46]. For PRODECIDE implementation, the development of objective, measurable criteria is a key aim (e.g. “Percentage of participants who completed all modules.”). Quality standards will be predefined and then refined and completed during process evaluation.

Data will be collected at various time points. An iterative process of collecting and analyzing qualitative data will allow exploring unexpected aspects in further interviews [42]. Data will be analyzed in accordance with the method of collection [44]. Descriptive statistics will be used for quantitative data. For qualitative data, a qualitative content analysis according to Mayring will be performed [47].

